### Randomization

In total, 75 sets of double-blind needles were prepared and placed in separate bags numbered 1-75 (25 sets of 40 penetrating acupuncture needles, 25 sets of 40 skin-touch acupuncture needles, and 25 sets of 40 no-touch acupuncture needles). Seventy-five participants were randomly assigned 1:1:1 to the penetrating needle group, the skin-touch needle group, or the no-touch needle group by an independent investigator using a random numbers table that was generated by the RAND function (Microsoft Office Excel 2007).

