#### Secondary Outcomes

Secondary outcomes include:

Pain intensity was measured by VAS at baseline, 24 hours, 72 hours, and one week after treatment.Physical disability assessed using the RMDQ at baseline and one week after treatment.Back pain–related quality of life assessed using the JOABPEQ at baseline and one week after treatment.Acupuncture sensation was assessed with the MASS immediately after treatment.Practitioner and participant guesses regarding needle authenticity immediately after treatment.

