### Secondary Self-Report Measurement

The following validated questionnaires were used to assess physical disability and acupuncture-related sensations at the specified time points.

RMDQ: the RMDQ assesses physical disability and was completed at baseline and one week after.JOABPEQ: the JOABPEQ assesses physical disability with social life and their psychological effects, and it was completed at baseline and one week after.MASS: the MASS consists of 12 descriptors of sensations to qualify and quantify acupuncture sensations. Participants select up to 12 descriptors that describe the sensations they had during their acupuncture treatment and then rate the intensity of these sensations on a numeric rating scale (NRS) from 0 (none) to 10 (strongest imaginable). If participants felt other sensations in addition to the 12 descriptors, they wrote a description of the additional sensation and rated it on the NRS [64,65]. The MASS was completed right after the acupuncture treatment was complete.Blinding assessment: the practitioner and patient guess at the needle’s authenticity. The participants guessed whether the needle type was “penetrating,” “skin-touch,” “no-touch,” or “cannot identify the needle type” right after the acupuncture treatment was complete. The acupuncturists were also asked to guess the needle type and rated their confidence in their guess.

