### Recruitment

Seven licensed, experienced acupuncturists (4 are listed as authors: [name]) with more than 5 years of experience each, at TAU Acupuncture Clinic, administered the acupuncture treatments. We enrolled 75 participants with CNSLBP. Participants were recruited by advertisements listed on TAU websites, flyers placed on TAU campus notice boards, and at public facilities (city offices, gymnasiums, and surrounding high-rise apartment buildings). The advertisements provided a brief introduction to the study, a description of the target population with eligibility criteria, and study contact information. Participant recruitment began in October 2018.

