### Statistical Analysis

Baseline characteristics will be assessed using Fisher exact test, ANOVA, and the Levene test. To evaluate the primary and secondary outcomes, we will use a linear mixed-effects model to account for the variability between groups and over time. This model will include “treatment group,” “time,” and their interaction as fixed effects. To address the potential influence of practitioner-related differences, “practitioner ID” will be included as a random effect. For post-hoc analyses, the Bonferroni correction will be applied to adjust for multiple comparisons. For nonnormally distributed data, the Mann-Whitney *U* test, Friedman test, or Kruskal-Wallis test will be used as appropriate. Blinding success will be evaluated by comparing the proportion of correct guesses in each group against chance level (33.3%) using a chi-square goodness-of-fit test. In addition, Bang Blinding Index will be calculated for both participants and acupuncturists to quantify the degree of blinding [55,57]. A Blinding Index close to 0 indicates successful blinding, whereas values approaching ±1 indicate unblinding. To account for variability among acupuncturists, analyses will be conducted under an intention-to-treat framework. Missing outcome data will be handled using multiple imputation under the assumption of missing at random. All statistical analyses will be conducted using SPSS Statistics version 31 (IBM SPSS Statistics) and R (R Foundation for Statistical Computing). Statistical significance will be set at a 2-sided *P* value of <.05.

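### The per-arm chi-square blinding test takes each guess as independent, but the 75 acupuncturist guesses come from seven people, so it can flag intact practitioner blinding more often than 5%

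*Protocol article*

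**What the plan says.** Blinding is assessed by "comparing the proportion of correct guesses in each group against chance level (33.3%) using a chi-square goodness-of-fit test" (Statistical Analysis). The next sentence adds that the "Bang Blinding Index will be calculated for both participants and acupuncturists to quantify the degree of blinding". The Secondary Outcomes section lists "Practitioner and participant guesses regarding needle authenticity immediately after treatment", and Secondary Self-Report Measurement states that "The acupuncturists were also asked to guess the needle type and rated their confidence in their guess".

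On numbers, Recruitment states that "Seven licensed, experienced acupuncturists" gave the treatments and that "We enrolled 75 participants with CNSLBP". Randomization gives equal allocation: "Seventy-five participants were randomly assigned 1:1:1 to the penetrating needle group, the skin-touch needle group, or the no-touch needle group".

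For the outcome model the plan does allow for the practitioner: "To address the potential influence of practitioner-related differences, “practitioner ID” will be included as a random effect". That term belongs to the linear mixed-effects model. The model is said to serve primary and secondary outcomes, and guesses are listed as a secondary outcome. Blinding success, however, is given a separate test of its own, which has no practitioner term. A later sentence in the same section links acupuncturist variability to intention-to-treat analysis, which concerns who is analysed and in which arm, not the correlation of guesses.

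**The concern.** A goodness-of-fit test on 25 guesses per arm assumes 25 independent guesses. Participants meet this, because each guesses once. Acupuncturists need not. One who habitually answers penetrating will be right repeatedly in the penetrating arm and wrong repeatedly in the other two, with no leak of the allocation. If such habits differ between acupuncturists, the number correct in an arm varies more than the binomial variance allows, and the test rejects too often in both directions.

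At stake is how the practitioner-blinding result is read. Blinding the acupuncturist is the design feature the article stresses most, and a flagged arm could reflect a few habitual answerers rather than any failure of the needles.

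**Working it through.** **Inputs.** From the article: 7 acupuncturists, 75 participants, 25 per arm, null proportion 1/3, two-sided 5% level. Average load: 75/7 = 10.7 guesses per acupuncturist, and 25/7 = 3.57 per acupuncturist per arm. Assumed, because the article does not give them: the within-rater correlation ρ, the caseload split, and three forced answers for acupuncturists. The article states no error rate for the blinding test beyond the general 5% level, so there is no figure of its own to reproduce here.

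**Step 1: the test with independent guesses.** With k correct out of n = 25, the statistic is (k − n/3)² / (2n/9) = (k − 8.333)² / 5.556, compared with 3.841.
- k = 3 gives 28.44/5.556 = 5.12 (reject); k = 4 gives 18.78/5.556 = 3.38 (do not reject).
- k = 12 gives 13.44/5.556 = 2.42 (do not reject); k = 13 gives 21.78/5.556 = 3.92 (reject).

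The test therefore rejects at 3 or fewer, or 13 or more, correct. The exact binomial size is 5.6% per arm. For at least one of three arms it is 1 − (1 − 0.0564)³ = 16.0%.

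**Step 2: design-effect approximation.** DE = 1 + (25/7 − 1)ρ, and size = 2[1 − Φ(1.96/√DE)]. For ρ = 0.2, DE = 1 + 2.571 × 0.2 = 1.514 and the size is 11.1%. For ρ = 0.05, 0.1 and 0.5 it is 6.5%, 8.1% and 19.5%.

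**Step 3: simulation under perfect blinding.** Each of seven raters has personal answer probabilities drawn from a Dirichlet distribution with mean 1/3 per needle type and correlation ρ. Guesses ignore the arm, and 75 treatments are randomised 25/25/25 (20,000 runs per setting). A false failure is a rejection in either direction. Near-equal caseloads are 11, 11, 11, 11, 11, 10, 10; the unequal split, chosen for illustration, is 30, 15, 10, 8, 5, 4, 3.

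| ρ | Per arm, near-equal | At least one arm, near-equal | Per arm, unequal |
|---|---|---|---|
| 0 | 5.6% | 16% | 5.7% |
| 0.05 | 7.5% | 21% | 9.1% |
| 0.1 | 9.7% | 26% | 12.5% |
| 0.2 | 13.7% | 35% | 18.8% |
| 0.3 | 17.2% | 42% | 24.9% |
| 0.5 | 24.0% | 53% | 35.0% |

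The simulated rates exceed the approximation in Step 2, which assumes every acupuncturist's guesses split evenly over the arms and starts from 5.0% rather than the exact 5.6%.

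About 16 percentage points of every any-arm figure are present at ρ = 0. They come from running three unadjusted tests and not from clustering.

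**Step 4: tests that respect the rater.** A practitioner-stratified test of guess against arm (Cochran-Mantel-Haenszel type) rejects in 4.8% to 5.1% of runs per arm for ρ from 0 to 0.5, under both caseload splits. Its any-arm rate is 13% to 14%, since three tests remain. Permuting arm labels within practitioner, with total correct guesses as the statistic, rejects in 5.3%, 5.1% and 3.8% at ρ = 0.05, 0.2 and 0.5 (1,500 runs, 399 permutations each).

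**The case against.** **The target is inferred.** The chi-square sentence names no rater. If it is meant for participants only, the independence problem disappears. That stands as a caveat. But practitioner and participant guesses form one secondary outcome, and the Bang index sentence that follows is worded as an addition and names both. On the participants-only reading, the article gives no test for practitioner blinding.

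**Only an article is shown.** Rater clustering could be handled in a fuller plan. That would answer a complaint about missing detail. Here, however, the article fixes a named test that assumes independence.

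**The size is unknown.** This stands. Nothing in the article supports a particular ρ. At 0.05 with near-equal caseloads the excess is 7.5 − 5.6 = 1.9 points per arm. The acupuncturists read out a script describing three randomly assigned groups (Treatment Procedure). Raters who spread their answers evenly would have negatively correlated guesses and a conservative test. Their answer options are also not stated; the article lists options only for participants.

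**Stronger readings that are not supported.** A reader might infer that the practitioner test will fail far more often than 5%; the documents support only that it can. A reader might infer that the trial's efficacy results are at risk, but nothing in the article makes a primary conclusion depend on this check. Reporting all arms, with the Bang index, also gives a visible clue to habitual answering, since it raises correct guesses in one arm and lowers them in others. Finally, a reader might credit permutation with extra power. With 25% of guesses truly informed and ρ = 0.2, per-arm permutation and per-arm chi-square both have power of about 0.50. The gain comes from pooling: an ordinary chi-square on all 75 guesses reaches about 0.82 to 0.83, with a false-positive rate of 3% to 4%.

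**Conclusion.** The point holds in conditional form. If the test covers acupuncturists, and if they differ in guessing habits, the per-arm chi-square is miscalibrated for their guesses, and nothing in the article corrects it. Under three forced answers and near-equal caseloads, the excess over the 5.6% baseline runs from about 2 points per arm at ρ = 0.05 to about 18 points at ρ = 0.5 (24.0 − 5.6). It is larger with uneven caseloads, and absent or reversed if raters balance their answers. The any-arm rates should not be attributed to clustering alone. This is a minor point, limited to the practitioner half of a secondary blinding check; the participant blinding test and the two primary outcomes are unaffected.

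**What to change.** State in the Statistical Analysis section whose guesses each test covers. For acupuncturists, replace the per-arm chi-square with a permutation test: hold each acupuncturist's guesses fixed, permute arm labels within practitioner ID, and take total correct guesses as the main statistic, with per-arm results as support. A practitioner-stratified Cochran-Mantel-Haenszel type test of guess against arm is an acceptable alternative. Keep the chi-square for participants.

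Report the acupuncturist Bang index by arm descriptively, with a note that the guesses are clustered in seven raters. The permutation test does not itself yield an interval for the index. Resampling seven practitioners is too few to rely on: in a simulation of the per-arm correct proportion, nominal 95% percentile bootstrap intervals covered only 87% to 89%.

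The cost is a sentence or two and a short script in R, which the plan already names. Practitioner ID is already used in the outcome model and the guesses are already collected, so no new data are needed. The drawbacks are a less familiar test that is slightly conservative per arm, and one that cannot detect anything if every acupuncturist always gives the same answer.

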### Treatment Procedure

Before treatment, the acupuncturist read the following script to each participant, “You are going to be randomly assigned to one of three groups: the penetrating needle group, the skin-touch needle group, or the no-touch needle group. The penetrating needle group is the treatment using real acupuncture needles that penetrate the skin, the skin-touch needle group is the treatment using skin-touch acupuncture needles that touch the skin but do not penetrate, and the no-touch needle group is the treatment with no-touch acupuncture needles with tips that do not touch the skin.” All participants were given one free real acupuncture treatment upon the return of their surveys one week later. Individuals not meeting study inclusion criteria were also offered free acupuncture.

Next, the acupuncturist asked the participant to point out the most severe stiffness or pain in the lumbar, gluteal, and posterior thigh regions. Participants then lay supine on a treatment table.

Before each needle application, the acupuncturist massaged each acupoint with the fingertip of the index finger of the nondominant hand in a circular motion for 2 seconds. This insertion technique is a commonly practiced method in Japanese-style acupuncture. The assistant peeled off the adhesive paper covering the bottom of the pedestal of each needle device, covered the needle with an outer guide tube, and handed it to the acupuncturist. Then, the acupuncturist placed the needle device on the acupoint, which was held in place by the adhesive. The acupuncturist stabilized the needle device with the nondominant hand and tapped the top of the needle handle, which protruded from the outer guide tube, 5-7 times using the index finger of the dominant hand [66].

After needle tapping-in, the acupuncturist removed the outer guide tube and inserted the needle further to its targeted depth by rotating it clockwise and counterclockwise using an alternating twirling technique [38-45,54,66]. This process was repeated until all needles were inserted. The needles were retained for 15 minutes.

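### Blinding is scored by exact needle type, so naming the wrong placebo counts as blinded, and belief that the needle penetrated is never compared between arms

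*Protocol article*

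**What the plan says.** All references are to the protocol article.

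- **Guess options (Secondary Self-Report Measurement).** "The participants guessed whether the needle type was “penetrating,” “skin-touch,” “no-touch,” or “cannot identify the needle type” right after the acupuncture treatment was complete". Acupuncturists also guess the needle type.
- **Test (Statistical Analysis).** Blinding success is judged by "comparing the proportion of correct guesses in each group against chance level (33.3"%), with a chi-square goodness-of-fit test.
- **Index (Statistical Analysis).** "Bang Blinding Index will be calculated for both participants and acupuncturists to quantify the degree of blinding". The reading rule is "A Blinding Index close to 0 indicates successful blinding, whereas values approaching ±1 indicate unblinding". How the index is scored with three needle types is not stated.
- **What participants are told (Treatment Procedure).** The script describes one needle that pierces the skin and two that do not. For example, "the skin-touch needle group is the treatment using skin-touch acupuncture needles that touch the skin but do not penetrate".

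The Introduction gives the primary aim as comparing penetrating acupuncture with both placebo needles on FRP and pain intensity. No comparison of *penetrating* guesses with guesses of either placebo is stated.

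**The concern.** For the efficacy contrasts, the blinding question is whether the arms differ in the belief that the needle was real. Exact needle-type scoring answers a different question. A no-touch participant who answers *skin-touch* has correctly rejected the real needle, yet enters the test as an incorrect guess and pulls the result towards chance. The same holds for a skin-touch participant who answers *no-touch*, and for the acupuncturists' guesses.

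The article presents double-blinding as its main strength, and one co-primary outcome is a self-rated VAS recorded immediately after treatment. If the blinding check can pass in placebo arms where nobody believed the needle was real, it gives weaker support than it appears to for reading a VAS difference as a specific effect of penetration.

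**Working it through.** **Inputs.** 25 participants per arm (Sample Size); null proportion 33.3% in each group and two-sided 5% level (Statistical Analysis); three named needle types plus *cannot identify* (Secondary Self-Report Measurement). The split of guesses between the two placebo names is an assumption, because the article gives no guess data.

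**1. The plan's own figure.** One exact match among three named types gives 1/3 = 33.3%, which reproduces the stated chance level. Scoring real against either placebo would give 2/3 (or 1/2) in a placebo arm, and four equally likely options would give 25%. So 33.3% implies that *skin-touch* and *no-touch* are different answers.

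**2. What passes.** Chi-square = (x − n/3)² / (n × 1/3 × 2/3). With n = 25 this is (x − 8.333)² / 5.556.

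| Correct, x | Chi-square | p |
|---|---|---|
| 3 | 5.12 | 0.024 |
| 4 | 3.38 | 0.066 |
| 12 | 2.42 | 0.12 |
| 13 | 3.92 | 0.048 |

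An arm passes with 4 to 12 correct. In a placebo arm, 12 can name the right placebo and 13 the other, with none answering *penetrating*, and the test is still non-significant.

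**3. How often, if all placebo participants know it was placebo.** With an even split (assumed), correct guesses follow Binomial(25, 0.5). One placebo arm passes with probability 0.50, and both with 0.50² = 0.25. Variations:

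- 21 per arm: 0.67 and 0.45. 20 per arm: 0.59 and 0.35.
- Same placebo name preferred in both arms at 60:40: both pass with probability 0.13. At 70:30: 0.02. At 100:0: 0.
- 20% answer *cannot identify* and stay in the denominator, with the rest split evenly (assumed): 40% correct, giving 0.84 and 0.71. Again nobody answers *penetrating*.

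**4. Adding the penetrating arm.** It faces the same test. Its pass probability is 0.944 if the true rate of *penetrating* guesses there is 1/3, 0.844 at 40%, 0.50 at 50% and 0.154 at 60%. Multiplying by 0.25 from the even-split case, all three arms pass with probability 0.24, 0.21, 0.13 and 0.04 respectively.

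**5. Largest gap in belief that passes everywhere.** The penetrating arm passes with at most 12/25 correct, and a placebo arm can pass with 0/25 answering *penetrating*. The gap is 0.48 − 0 = 48 points. For a Newcombe interval, the Wilson limits are 0.300 to 0.665 for 12/25 and 0 to 0.133 for 0/25.

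- Lower: 0.48 − √(0.180² + 0.133²) = 0.26
- Upper: 0.48 + √(0.185² + 0²) = 0.67 (0.665 before rounding)

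**6. Bang index, if scored by exact match.** Index = (correct − incorrect)/n. Twelve of 25 correct gives (12 − 13)/25 = −0.04, and 13 of 25 gives +0.04. Both are near 0, the value the article reads as success. Random three-way guessing would give 1/3 − 2/3 = −0.33, so under this scoring the index and the 33.3% test have different benchmarks.

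**7. Same data with placebo answers pooled.** All 25 count as correct. The Bang index is +1, and chi-square against 2/3 is 12.5 (p = 0.0004). The unblinding is detected.

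**The case against.** The strongest reply is that the plan tests every arm, including the penetrating one. A reader might infer from the scoring problem that the arms could differ completely in belief and still be declared blinded. That is not so: 25/25 correct in the penetrating arm gives chi-square 50. Even 15/25 gives chi-square (15 − 8.333)²/5.556 = 8.0, p = 0.005, so a 60-point gap would be flagged as well. This stands, and it limits the point to gaps of 48 points or less.

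The two measures also partly cover each other. If 17 of 25 in each placebo arm answer *skin-touch* and the other 8 *no-touch*, the no-touch arm passes the test (8/25, p = 0.89), but its exact-match Bang index is (8 − 17)/25 = −0.36. The skin-touch arm, at 17/25, is flagged (chi-square 13.52, p = 0.0002). The near-zero index belongs to the even-split case.

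Exact-match scoring of the Bang index is an inference from the 33.3%; the article does not state it. The article also calls the item a guess at authenticity, which is compatible with real-versus-placebo scoring, and such detail may sit in a document not shown. The index part is therefore conditional. The 33.3% test is fixed in the text and is not.

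Two further inferences lack support. That no-touch participants are likely to answer *skin-touch* is conjecture without guess data. A gap in belief also cannot be converted into millimetres of VAS bias: the article gives no effect of belief on the VAS, and participants rate pain before they guess, so the guess may partly reflect felt relief.

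Finally, exact-type identification has a use, since the aims also compare the three needles with one another. That is a reason to keep it as a secondary measure. It does not make it a measure of belief in the real needle.

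**Conclusion.** The point holds for the stated chi-square rule. Exact-type scoring counts a correct rejection of the real needle as a wrong guess whenever the other placebo is named, and the comparison that bears on the efficacy contrasts is not among the stated analyses. A placebo arm in which nobody believed the needle was real passes with 4 to 12 of 25 correct, and the test can pass in all arms with belief in penetration as far apart as 12/25 versus 0/25.

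This shows that the check can fail to detect unblinding, not that it will. The 0.50 and 0.25 probabilities rest on all placebo participants knowing and on an even split, and they fall quickly if one placebo name is preferred in both arms. The efficacy model does not use the blinding result. What is at stake is the conclusion on blinding, and through it the interpretation of the VAS co-primary. The change should be made because that conclusion could differ and the cost is very small.

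**What to change.** In Statistical Analysis, make belief in penetration the main blinding measure:

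- Report the proportion answering *penetrating* in each arm, and the difference between the penetrating arm and each placebo arm with its 95% CI.
- Compute the Bang index on guesses collapsed to *penetrating*, *not penetrating* and *cannot identify*, and state this scoring.
- Do both for participants and, from their needle-type guesses, for acupuncturists.
- Keep exact needle-type identification as a secondary measure, for skin-touch versus no-touch, and say how *cannot identify* enters its denominator.

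The cost is a few lines of analysis wording. The guesses are already collected, so no new data or participants are needed.
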